## Abstract

**Background:**

Pruritus (itch) is a frequent, burdensome and difficult-to-treat symptom in patients with cholestasis. Fibrates are currently under investigation for the treatment of primary biliary cholangitis in patients with a suboptimal response to ursodeoxycholic acid. Moreover, there is empirical evidence for a possible antipruritic effect. We aim to prove this in a randomized controlled trial, including patients with cholestatic liver diseases other than primary biliary cholangitis that are accompanied by pruritus.

**Methods:**

A multicenter investigator-initiated, double-blind, randomized placebo-controlled trial to evaluate the effect of bezafibrate on cholestatic pruritus in 84 adult patients with primary biliary cholangitis or primary/secondary sclerosing cholangitis. Primary outcome is the proportion of patients with a reduction of itch intensity of 50% or more (measured on a Visual Analog Scale) after 21 days of treatment with bezafibrate 400 mg qid or placebo. Secondary outcomes include the effect of bezafibrate on a five-dimensional itch score, liver disease-specific quality of life, serum liver tests and autotaxin activity. Safety will be evaluated through serum parameters for kidney function and rhabdomyolysis as well as precise recording of (serious) adverse events. We provide a schematic overview of the study protocol and describe the methods used to recruit and randomize patients, collect and handle data and perform statistical analyses.

**Discussion:**

Given its favorable safety profile and anticholestatic properties, bezafibrate may become the new first-line treatment option for treating cholestatic pruritus.

**Trial registration:**

Netherlands Trial Register, ID: NCT02701166. Registered on 2 March 2016;

Netherlands Trial Register, ID: NTR5436. Registered on 3 August 2015.

**Electronic supplementary material:**

The online version of this article (doi:10.1186/s13063-017-1966-8) contains supplementary material, which is available to authorized users.

## Background

A wide variety of cholestatic conditions are associated with pruritus (itch), including primary biliary cholangitis (PBC, formerly referred to as primary biliary cirrhosis [1]) and primary sclerosing cholangitis (PSC). The pruritus can occur locally or be generalized and is often reported by patients as the most burdensome symptom of their disease. Treatment options are limited as the pathophysiologic mechanism is largely unknown [2]. In our experience, resistant cases report severe sleep deprivation, depression and even suicidal ideations. In some patients, liver transplantation turns out to be the only option left [3].

### Fibrates in cholestatic liver diseases

Ursodeoxycholic acid (UDCA) is the only FDA- and EMA-approved therapy for PBC, improving transplantation-free survival. UDCA-responsive patients generally have similar life expectancy as sex- and age-matched controls [4]. Still, about 40% of patients do not respond to UDCA. Complementary treatment strategies are thus needed. In recent years, several case reports and pilot studies describe improvement of serum liver function tests upon fibrate treatment in patients with a suboptimal response to UDCA [5–20]. Whether or not fibrates improve transplantation-free survival in addition to UDCA remains to be proven in a currently ongoing phase III trial in PBC patients (www.clinicaltrials.gov: NCT01654731). Importantly, UDCA does not show benefit for pruritus in PBC and PSC. According to clinical observations [21], in line with some of the abovementioned reports [14, 17, 22, 23], bezafibrate does potentially have antipruritic properties. Anecdotally, itch complaints occur or recur after stopping the fibrates [21, 22].

### Bezafibrate as a potential alternative to current guideline-recommended antipruritic therapies

Rifampicin, the best available evidence-based treatment for the itch of cholestasis [4, 24, 25], has the disadvantage of hepatotoxicity in up to 12% [26–32] of patients with cholestasis during prolonged treatment. Moreover, rifampicin induces a wide variety of cytochrome P-450 (CYP) enzymes and, therefore, interacts with many different drugs. Fibrates would thus be an attractive alternative treatment for itch as they seem to be safe for long-term administration and seem to provide additional benefits to the course of the disease (at least, for PBC). Other treatment strategies are not as effective as rifampicin (e.g., bile salt sequestrants, naltrexone) or are experimental and much more invasive (e.g., nasobiliary drainage, plasmapheresis, ultraviolet-B phototherapy, liver transplantation) [4].

### Aim of this study: to evaluate the antipruritic effect of fibrates

The itch-relieving effect in the abovementioned studies was not measured as a primary outcome and was thus not systemically objectified by current quantification methods for itch intensity such as the widely used Visual Analog Scale (VAS) (validated in [33], discussed in [34]). Moreover, antipruritic effects were not controlled for while a considerable placebo effect should be taken into account (about 30% itch reduction was seen upon placebo treatment in one study [35]). Thus, we would like to validate the promising effect of fibrates on itch as a primary outcome in a double-blind, randomized placebo-controlled study.

### Proposed molecular antipruritic effect(s) of bezafibrate

As an agonist of peroxisome proliferator-activated receptors (PPARs), bezafibrate has anti-inflammatory [36–38], anticholestatic [20, 39–42] and antifibrotic [43] properties. In the current study we hope to identify its antipruritic mode of action. Our group recently showed that serum levels of lysophosphatidic acid (LPA) and serum autotaxin (ATX) activity, the enzyme forming the bulk of extracellular LPA, correlate with itch intensity in patients with cholestasis [44]. Our working hypothesis is that during cholestasis, increased serum ATX activity causes an increase in LPA-mediated activation of itch-specific sensory nerve endings. Importantly, successful guideline-approved and experimental antipruritic treatments (rifampicin, nasobiliary drainage and albumin dialysis) in patients with cholestasis correlated with a decline in serum ATX activity levels [45]. Thus, secondary objectives of the current study are determination of the effect of bezafibrate on serum ATX activity levels and/or screening for other pruritogens.

### Objectives

The primary objective is to determine the efficacy of bezafibrate in the treatment of moderate to severe cholestatic pruritus. Secondary objectives include efficacy in improvement of fatigue and liver disease-related quality of life and reduction of serum parameters of cholestasis, cholesterol, triglycerides and autotaxin activity. Safety will be evaluated through recording of (serious) adverse events ((S)AEs) and (suspected unexpected) adverse reactions ((SU)SARs) as well as serum parameters for kidney function and rhabdomyolysis. Also, the effect of stopping treatment on all the abovementioned variables will be assessed.

### Trial design

This is a multicenter, investigator-initiated, double-blind, randomized placebo-controlled trial.

## Methods

Methods are described according to the Standard Protocol Items: Recommendations for Interventional Trials (SPIRIT) 2013 Checklist for interventional trials which is provided in Additional file 2.

### Study setting

A total of nine academic hospitals are participating in this study, eight in the Netherlands and one in Spain (Barcelona). A list of study sites is provided at www.clinicaltrials.gov: NCT02701166.

### Inclusion criteria

Patients of 18 years or older with primary biliary cholangitis (PBC), primary sclerosing cholangitis (PSC) or secondary sclerosing cholangitis (as defined in the clinical practice guidelines of cholestasis from 2009 by the European Association for the Study of the Liver (EASL) [4]) can be included if they report an itch intensity of at least 5 out of 10 cm on a VAS twice within the week before inclusion with a minimum of 2 and a maximum of 7 days between both itch scores.

### Exclusion criteria

Subjects meeting any of the following criteria will be excluded from participation:Primary dermatologic abnormalities associated with pruritusConcomitant guideline-recommended as well as experimental antipruritic therapy, e.g., rifampicin, opioid-receptor antagonists (naltrexone, naloxone), serotonin-reuptake inhibitors (sertraline), ondansetron, phenobarbital, propofol, lidocaine, dronabinol, butorphanol, internal or external biliary drainage, extracorporeal albumin dialysis, ultraviolet-B phototherapyNB. Topical menthol-containing agents are allowed, as well as bile salt sequestrants (colesevelam, cholestyramin) as long as they are taken at least 4 h before or after intake of the study medication. Incidental use of these agents should be noted by patients in the diary, structural use should be noted on the Case Report Form (CRF)Pregnancy, women of childbearing potential not using contraception, breastfeedingCholestasis due to obstruction that requires invasive desobstructive treatment within the time scope of the study (5 weeks) such as endoscopic retrograde cholangiopancreaticography (ERCP) or surgical removal of a tumor compressing the bile ductUse of opiatesRenal insufficiency (creatinine clearance <60 mL/min)N.B. Concomitant use of UDCA is allowed

### Study interventions

Placebo tablets were developed matching the licenced Bezalip® Retard 400 mg Actavis tablets. The composition of the placebo tablets consists mainly of lactose monohydrate and excipients used were similar to the excipients of the uncoated Bezalip® Retard 400 mg Actavis tablets. Placebo tablets were manufactured under Good Medicinal Practice (GMP) licence.

Additional file 3 provides a flow diagram of the study protocol. Additionally, a schematic overview according to the SPIRIT guidelines is provided in Fig. 1. Participation requires three 30-min outpatient clinic visits during the course of the study: at day 0 (start of treatment, bezafibrate or placebo), days 21 (end of treatment) and 35 (follow-up 2 weeks after stop of treatment).

**Fig. 1 Fig1:**
[figure not shown]
Standard Protocol Items: Recommendations for Interventional Trials (SPIRIT) figure: schedule of enrollment, interventions and assessments. *5D* five-dimensional, *LDSI* Liver Disease Symptom Index, *VAS* Visual Analog Scale

### Criteria for withdrawal of study subjects

Increase in serum transaminases (alanine aminotransferase (AST), alanine aminotransferase (ALT)) above six times the upper limit of normal *or* an increase of three or more times compared to the start of treatmentIf serum creatinine is within the normal range at the start of the study, an increase above 133 μmol/L is considered a reason for withdrawal. In case serum creatinine is increased already at start of the study we will allow an increase of 50% of serum creatinine concentration

### Procedures to monitor adherence to treatment

Tablets remaining after the treatment phase of the intervention will be used to assess adherence to treatment. Moreover, serum cholesterol and triglyceride levels will be tested, reflecting treatment adherence in the bezafibrate-treated group.

### Outcomes

#### Visual Analog Scale (VAS) itch score

The primary endpoint will be calculated from VAS scores obtained at study visits 1 and 2 (at start and stop of therapy), asking patients to report the maximum itch intensity of the past 24 h. We are using VAS itch scores as it is the most widely used method to assess itch intensity [33]. The scale consists of a 10-cm horizontal line divided into ten equal parts numbered 0 to 10. The 0 on the left is accompanied by a smiling face and the text “no itch at all,” the 10 on the right is accompanied by a sad-looking face and the text “worst itch possible.” Mostly to promote treatment fidelity, during the 21-day treatment period, patients will be asked to keep a diary to score their itch intensity (VAS) twice daily (after waking up in the morning and before going to bed in the evening) and make notes such as the use of co-medication, side effects and other information.

#### Five-dimensional (5D) Pruritus Scale

The 5D Pruritus Scale [46] is increasingly used in pruritus research, probably more accurately reflecting itch complaints as it evaluates multiple dimensions of itch during the course of the past 2 weeks: in addition to itch intensity (*degree,* range 1 (not present) to 5 (unbearable)), it assesses *duration* (range 1 (less than 6 h a day) to 5 (all day) and *direction* (range 1 (itch completely resolved) to 5 (getting worse). *Disability* is rated by the extent to which itch interferes with sleep (range 1 (never affects sleep) to 5 (delays falling asleep and frequently wakes me up at night) and social/leisure activities, homework/errands and professional activities (school/work) (all range 1 (never affects this activity) to 5 (always affects this activity)). *Distribution* is assessed by marking the affected skin surfaces on a ventral and dorsal body drawing which is an adaption made to the original version of the 5D Pruritus Scale where a list of body parts was listed in order to check affected sites. This way, we aim to calculate the extent of pruritic skin as a percentage of the whole body surface by the “rule of nine,” a method widely used to diagnose burn wound surface [47].

#### Liver Disease Symptom Index (LDSI) version 2.0

The LDSI2.0 [48] is a short questionnaire used to assess the potential effects of bezafibrate on other liver disease-related symptoms. It contains 18 questions regarding complaints of arthritis, pruritus, fatigue, abdominal pain, anorexia, jaundice and psychosocial consequences of the disease including depression and anxiety. Complaints can be rated on a 5-point scale; total score ranges from 18 to 90, higher scores reflecting worse symptoms.

#### Biological specimens

Serum will be collected from each participant at three time points: day 0, day 21 and day 35. Measurements of serum cholestasis parameters, including bilirubin, alkaline phosphatase (AP), gamma glutamyltransferase (γGT), ALT, AST, as well as albumin, lactate dehydrogenase (LDH), creatinine kinase (CK), low- and high-density lipoprotein (LDL, HDL) and total cholesterol, will be measured at the sites’ diagnostic laboratories. Furthermore, sample aliquots will be collected and stored at −80 °C until the last patient has completed the trial. Samples will be shipped on dry ice to the principal investigator’s laboratory.

Autotaxin (ATX) activity will be measured using an enzymatic endpoint assay, in which the amount of choline produced after 60 min of incubation of the sample with 1 μM of the substrate of ATX, lysophosphatidylcholine (LPC), is detected by fluorescence. Bile acid species will be determined using high-performance liquid chromatography (HPLC).

### Sample size calculation

We will compare the proportion of patients from both treatment arms who show a clinically relevant response to treatment which is defined as a reduction in itch intensity of at least 50%. Based on former placebo-controlled trials for cholestatic itch, selecting data only from patients with itch scores of 5 or higher at baseline who were treated for at least 2 weeks, we estimated that 18% of placebo-treated patients will show the defined response [30, 35, 49–51]. Based on empiric observations we believe that at least 50% of bezafibrate-treated patients will respond. Thus, we anticipate a difference in proportions between the bezafibrate and placebo groups of 32%.

Using Fisher’s exact test with alpha set at 0.05 we need 38 patients per group for a power of 0.80 for two-sided testing. Taking into account a 10% possible dropout we will include 84 patients (42 per arm) in this study. This power calculation was made after consulting a statistician and using the statistical program nQuery Advisor version 3.0.

### Recruitment

Patients are recruited from outpatient clinics of participating academic medical centers. After informed consent, based on oral and written information (see Additional file 1) provided by study physician or nurse, patients are enrolled at day 0 if the itch intensity is at least 5 out of 10 on a VAS, and all other inclusion and exclusion criteria are met. For all patients who drop out before day 21, we will include a replacement, whereas patients dropping out during the follow-up phase will not be substituted (see also Additional file 3).

The first participant was enrolled in April 2016. Recruitment is expected to be completed in 18 months, and will be enhanced by creating awareness among clinicians through regular presentation of the trial at (inter)departmental meetings. Moreover, we keep close contact with patient organizations to advertise the trial.

### Randomization and blinding

After informed consent, patients will be allocated randomly to either bezafibrate or placebo treatment (ratio 1:1) as per a computer-generated randomization schedule with randomly varying block sizes (maximum block size of 4) by the sites’ investigator through a web-based module written in ALEA (https://nl.tenalea.net, copyright NKI AVL, Amsterdam) by the AMC Clinical Research Unit. Stratification takes place for the VAS itch score at day 0 (2 strata: 5 cm ≤ VAS < 7.5 cm versus 7.5 cm ≤ VAS ≤ 10 cm). An automated email with the resulting randomization number will be sent to the trial pharmacy which allocates the patient to one of the two treatment arms and distributes the study medication accordingly to the patients, using identical packaging for placebo and bezafibrate tablets. This way, patients, physicians and outcome assessors stay blinded for treatment allocation. All investigators are aware that the pharmacy keeps the randomization list locked until all patients have completed the study, and that a request for unblinding can only be done in case a serious adverse event (SAE) occurs. Investigators at all sites keep their own subject identification log, in a secure place, and handle all personal data according to the local regulations on personal data protection.

### Data collection and management

Data collection will take place using electronic Case Report Forms (eCRFs, written by the coordinating investigator using web-based OpenClinica software (www.openclinica.com)) for the three visits, with built-in range checks for most variables. An appointed, independent monitor verifies entry of data on a regular basis by site visits according to a detailed monitoring plan.

From the data collection tool, data can be exported directly to the database software (SPSS). The coordinating investigators manage coded data by regular backups on a secure drive. Site agreements have been signed by coordinating and participating centers to assure agreement about access to, and use of, trial data.

### Statistical analysis plan

Statistical analyses will be performed using SPSS (version 22 or above) according to intention-to-treat principle: patients who dropped out before the end of treatment because of lack of treatment efficacy will be included in sensitivity analyses. The nature and extent of any missing data and coding/typing errors will be addressed in a blinded fashion and dealt with accordingly following general principles (e.g., imputation and/or the use of specific statistical models), as will be described in the resulting manuscript.

Statistical tests will be two-tailed. *P* values < 0.05 will be considered as statistically significant. Baseline characteristics of the study population in both groups will be depicted in a table, summarizing means ± standard deviations of continuous variables and frequencies and proportions (%) for categorical variables. The primary outcome measure will be depicted in a graph. Specific statistical methods to analyze the most important outcome measures are addressed below. Results of these analyses (% change in each group, *P* values) will be presented in a table.

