#### Primary outcome

The effect of bezafibrate on itch will be confirmed by a Fisher’s exact test on the difference in the proportion of patients responding to treatment (≥50% reduction of itch intensity in the VAS score at day 21 compared to day 0) between the bezafibrate and the placebo groups.

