#### Interim analysis

As we are not studying an intervention for life-threatening disease, no interim analysis will be performed to be able to keep investigators blinded until all 84 patients have completed the study.

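### Intention-to-treat is named, but lack-of-efficacy dropouts go to sensitivity analyses and all pre-day-21 dropouts are replaced, so the primary set is contradictory and most naturally read as completers

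*Protocol article*

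**What the plan says.** All references are to the protocol article.

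- **Statistical analysis plan:** names the intention-to-treat principle and, after a colon, explains it: "patients who dropped out before the end of treatment because of lack of treatment efficacy will be included in sensitivity analyses". It adds that missing data will be examined blinded and "dealt with accordingly following general principles (e.g., imputation and/or the use of specific statistical models), as will be described in the resulting manuscript".
- **Recruitment:** "For all patients who drop out before day 21, we will include a replacement". Patients lost in the follow-up phase after day 21 are not replaced.
- **Randomization and blinding:** allocation follows consent and is stratified by the day-0 VAS. A patient who leaves between day 0 and day 21 is therefore a loss after randomisation.
- **Primary outcome:** Fisher's exact test on the proportion with at least a 50% fall in VAS from day 0 to day 21. The section does not say how a patient without a day-21 score is classed.
- **Sample size calculation:** 38 per group for power 0.80 at 18% versus 50%, and then "Taking into account a 10% possible dropout we will include 84 patients (42 per arm) in this study".
- **Interim analysis:** investigators stay blinded "until all 84 patients have completed the study".

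**The concern.** Under intention-to-treat, a patient who leaves because the treatment does not work belongs in the primary analysis. For a responder endpoint, that patient is the clearest kind of failure. The plan instead assigns these patients to sensitivity analyses and fills their places with new recruits.

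Leaving early is likely to be related to outcome here. The Discussion asks participants to use no rescue medication other than topical agents and bile sequestrants, so a patient with uncontrolled itch has a reason to stop. If such patients are outside the confirmatory test, the arms compared are no longer the arms randomised.

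The Discussion rests the whole strategy against multiplicity on this single confirmatory endpoint, so the primary set has to be unambiguous. The sample size raises a related question: the 10% allowance and the replacement rule both compensate for the same losses.

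**Working it through.** **1. The plan's own figure.** Inputs from Sample size calculation: 18% versus 50%, two-sided alpha 0.05, Fisher's exact test. Power is the sum, over all pairs (a, b), of Bin(a; n, 0.18) × Bin(b; n, 0.50) × 1[Fisher p < 0.05].

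- n = 37 per arm: 0.785
- n = 38 per arm: 0.800

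The stated 38 per arm reproduces and is not in dispute.

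**2. Reading the sections together.** Lack-of-efficacy dropouts are placed in sensitivity analyses. Every pre-day-21 dropout is replaced. Response requires a day-21 VAS. Blinding lasts until all 84 have completed. The set that fits all four statements is 84 completers, which does not fit the intention-to-treat label.

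**3. Effect on an arm's response proportion.** Let p be the response rate among all randomised and x the share of non-responders who leave and are replaced. The completer rate is p / [p + (1 − p)(1 − x)].

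- p = 0.18, x = 0.20: 0.18 / (0.18 + 0.82 × 0.80) = 0.18 / 0.836 = 0.215
- p = 0.18, x = 0.30: 0.18 / (0.18 + 0.82 × 0.70) = 0.18 / 0.754 = 0.239

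**4. Type I error.** True rate 18% in both arms, 42 completers per arm, losses in one arm only, same enumeration:

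| Non-responders lost in one arm | Completer rates | P(reject) |
|---|---|---|
| none | 0.180 / 0.180 | 0.029 |
| 20% | 0.180 / 0.215 | 0.043 |
| 30% | 0.180 / 0.239 | 0.066 |

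If both arms lose 20%, the rates are 0.215 / 0.215 and P(reject) is 0.030. The harm comes from unequal loss.

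**5. Power under 50% versus 18%.** With 42 completers per arm and no selective loss, power is 0.844. If only placebo loses 20% of its non-responders, the rates are 0.50 versus 0.215 and power is 0.730.

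**6. How few patients matter.** Take an assumed result of 17/42 versus 8/42 (bezafibrate versus placebo) with everyone counted, and then remove non-responders:

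| Removed (bezafibrate, placebo) | Table | Fisher p |
|---|---|---|
| none | 17/42 vs 8/42 | 0.055 |
| 4, 4 | 17/38 vs 8/38 | 0.0497 |
| 4, 2 | 17/38 vs 8/40 | 0.029 |
| 2, 4 | 17/40 vs 8/38 | 0.054 |
| 0, 4 | 17/42 vs 8/38 | 0.091 |

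**7. The meaning of 84.** Sample size calculation: 42 × 0.90 = 37.8, so 84 enrolled should yield about 38 evaluable per arm. Interim analysis: 84 complete. With 10% loss, 84 completers need 84 / 0.90 = 93.3, or about 94 randomised. Both cannot be the design.

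**8. Power when all randomised patients count, 42 per arm.**

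- If 50% and 18% are rates among all randomised: 0.844.
- If they are completer rates and 10% drop out as non-responders, the rates are 0.50 × 0.90 = 0.45 and 0.18 × 0.90 = 0.162, and power is 0.776.

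**The case against.** The strongest reply is that no sentence says the primary test uses completers only, or that a replaced patient leaves the analysis. If replacements are extra randomised patients and the originals stay in, randomisation is intact. The missing-data sentence also leaves imputation open, which could cover patients who leave for adverse events or under the laboratory withdrawal criteria. This stands in part: completers are the natural joint reading, not a stated definition, and one cannot say that the other dropouts appear in no analysis. It does not rescue the text, because an unspecified imputation does not override the explicit placement of lack-of-efficacy dropouts in sensitivity analyses.

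A reader might infer that the rule favours bezafibrate. The documents do not support that. If placebo loses more failures, which is plausible when patients leave for lack of efficacy, the difference shrinks, as the power loss in step 5 and the last row of step 6 show.

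A reader might also infer that the sample size is wrong or the power overstated. It is not shown to be. Replacing dropouts on top of the allowance can only help power, and 0.776 applies only if the planning rates are completer rates, which the article does not say.

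Finally, the choice of missing-data method is commonly left to an analysis plan, and the full one is not shown. Its absence here is not part of this point.

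**Conclusion.** The point holds as a contradiction in the stated rules. Following them as written would most naturally leave known treatment failures out of the only confirmatory test, under an intention-to-treat label. The response proportion is biased upwards in any arm that loses non-responders. The direction of bias in the comparison cannot be known in advance.

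The size depends on dropout patterns that the documents do not give. Loss of 20% of one arm's non-responders leaves type I error below 0.05, because Fisher's test is conservative here; loss of 30% takes it above. Balanced loss does almost no harm to type I error. These figures assume that only non-responders leave selectively and that 42 per arm complete.

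The double meaning of 84 is a secondary inconsistency. It leaves the randomised number undefined but is not an error in the power calculation.

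This should be settled before unblinding, since it determines who is in the confirmatory comparison.

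**What to change.** 1. Define the primary set as all randomised patients in their allocated arm.
2. Count lack-of-efficacy dropouts, and any other patient without a day-21 VAS, as non-responders. Other prespecified handling could be defended for the remaining dropouts, but lack-of-efficacy dropouts should count as failures in the primary test.
3. Make the completer analysis, and multiple imputation if wanted, sensitivity analyses.
4. The replacement rule may stay if replacements are described as additional randomised patients and the replaced patients remain in the analysis.
5. State whether 84 is the number randomised or the number completing, make the three sections agree, and state power to match. With 84 randomised it is 0.844 if 50% and 18% are rates among all randomised, or about 0.78 if they are completer rates with 10% dropping out as non-responders.

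Fisher's test need not change. The cost is wording, with no extra patients required by the repair itself. The downside is that the reported response rates, and possibly the power, become slightly less favourable.

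### The confirmatory test is labelled intention-to-treat, but the rules on dropouts and replacements make it in effect a completer comparison

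*Protocol article*

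**What the plan says.** All references are to the protocol article.

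- **Statistical analysis plan.** Analyses are to follow intention-to-treat. After a colon, the only explanation offered is that "patients who dropped out before the end of treatment because of lack of treatment efficacy will be included in sensitivity analyses". The next sentence says that missing data will be examined blind and handled by general principles, with examples given as "imputation and/or the use of specific statistical models), as will be described in the resulting manuscript".
- **Recruitment.** "For all patients who drop out before day 21, we will include a replacement", whatever the reason for leaving. Losses after day 21 are not replaced.
- **Interim analysis.** Blinding is kept until all 84 patients have completed.
- **Primary outcome.** Response is a fall in VAS of at least half from day 0 to day 21, compared between arms by Fisher's exact test. No status is given to a patient without a day-21 score.
- **Sample size calculation.** "Using Fisher’s exact test with alpha set at 0.05 we need 38 patients per group for a power of 0.80 for two-sided testing", and then "Taking into account a 10% possible dropout we will include 84 patients (42 per arm) in this study". The assumed rates are that "we estimated that 18% of placebo-treated patients will show the defined response" and that "at least 50% of bezafibrate-treated patients will respond".

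**The concern.** Under intention-to-treat, patients who leave for lack of efficacy belong in the primary test, and sensitivity analyses vary how they are handled. Here they are named for sensitivity analyses, their places are filled by new patients, and 84 serves as a count of completers although it already contains a dropout allowance. The natural reading is that the main Fisher test compares 42 completers with 42 completers.

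That matters because a patient who stops when the itch has not improved has failed on this endpoint. Leaving the patient out, and recruiting someone who may respond, raises the arm's response rate. The Discussion makes this the only confirmatory comparison, so a result reported as intention-to-treat would not be one.

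**Working it through.** **1. The plan's own figure.** Inputs from the Sample size calculation: 18% v 50%, two-sided alpha 0.05, Fisher's exact test. Power is the sum, over all pairs of responder counts, of the product of the two binomial probabilities wherever the Fisher P value is below 0.05. With 37 per arm this gives 0.785, and with 38 per arm 0.800. The stated 38 reproduces. Adding 10% gives 38 × 1.10 = 41.8, or 42 per arm and 84 in total, as stated.

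**2. Effect of leaving failures out.** Let r be the response rate among all randomised patients and d the proportion of the arm that leaves before day 21. *Assumption:* everyone who leaves is a non-responder. The rate among completers is then r/(1 − d). The document gives only an overall 10% dropout, so the splits between arms below are assumptions.

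*Planned effect, 50% v 18% (true difference 32 points):*

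| Failure loss, bezafibrate v placebo | Completer rates | Difference |
|---|---|---|
| 10% v 10% | 0.50/0.90 = 55.6% v 0.18/0.90 = 20.0% | 35.6 points |
| 20% v 0% | 0.50/0.80 = 62.5% v 18.0% | 44.5 points |
| 0% v 20% | 50.0% v 0.18/0.80 = 22.5% | 27.5 points |

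With 42 completers per arm, power in the last row is 0.695, against 0.844 with no loss. The bias can therefore work for or against bezafibrate. Equal loss still widens the gap, because dividing by 0.90 adds more to the larger rate.

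*No drug effect, 42 completers per arm after replacement; probability that Fisher's test rejects:*

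| Failure loss, bezafibrate v placebo | 18% response in both arms | 30% response in both arms (assumed) |
|---|---|---|
| 0% v 0% | 2.9% | 3.0% |
| 10% v 0% | 3.3% | 3.9% |
| 20% v 5% | 4.3% | 5.9% |
| 20% v 0% | 5.1% | 7.7% |

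**3. A borderline result.** Suppose six bezafibrate patients leave as failures and are replaced, and none leave placebo. Completers: 21/42 v 10/42, P=0.023. With the six restored as non-responders: 21/48 v 10/42, P=0.075. Six of 90 randomised is 6.7% overall, but 6/48 = 12.5% of one arm. All six are needed: with five restored, 21/47 v 10/42 gives P=0.047.

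**4. Power if all randomised patients are analysed, 42 per arm.** If 18% and 50% are rates among all randomised: 0.84. If they are completer rates and 10% of each arm leave as failures, the rates become 0.90 × 18% = 16.2% and 0.90 × 50% = 45%, and power is 0.78.

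**The case against.** The best reply is that the plan never says these patients are excluded from the primary test. Inclusion in sensitivity analyses does not strictly mean inclusion there alone, and replacing a patient does not by itself remove the one replaced. The sentence on missing data covers all missing values, so imputation could return dropouts of any kind to the main test. This stands as far as it goes: exclusion is an inference from several sections. But on the kinder reading the text still does not tell the reader who is in the Fisher test, and the one clause that explains intention-to-treat does not deliver it.

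Four stronger readings might be inferred, and the document does not support them:

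- **That the false-positive rate is seriously inflated.** Fisher's test is conservative here and absorbs the bias at 10% v 0% loss. Rates above 5% need larger and unequal losses that nothing in the document predicts. If placebo patients are the ones who leave for lack of efficacy, the bias works against bezafibrate.
- **That leaving the missing-data method open is itself a defect.** A condensed article commonly leaves such detail to the full protocol or analysis plan, and blinded handling is a real safeguard.
- **That imputation cannot be used with Fisher's test.** That difficulty belongs to multiple imputation. Single imputation, including counting dropouts as non-responders, gives one table and one P value.
- **That the trial is wrongly sized.** The 38 per arm reproduces, and a dropout allowance is ordinary practice.

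The reversal in step 3 is also deliberately one-sided. It shows what can happen, not what is likely.

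**Conclusion.** Wrong as written. The intention-to-treat label and the rules that follow it do not agree. Taken with replacement and the wait for 84 completers, they point to a completer comparison as the only confirmatory test. The consequence is moderate: little effect on type I error at the planned dropout, a distorted effect estimate (32 to 35.6 points at 10% failure loss in each arm, in either direction when losses are unequal), and a possible change of conclusion when the result is borderline and the losses fall in one arm. These sizes rest on the assumptions that every dropout is a non-responder and that the losses split between arms as shown.

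**What to change.** **Statistical analysis plan:** state that the primary Fisher test includes every randomised patient in the assigned arm, and that a patient without a day-21 VAS counts as a non-responder. This should hold at least for those who leave for lack of efficacy. If another rule is preferred for other reasons for leaving, name it and fix it before unblinding. Make the completer comparison, and imputation of the day-21 score from the diary scores, the sensitivity analyses.

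**Recruitment:** state that replacements are added to the denominator and do not take the place of patients who left.

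**Sample size calculation:** no change is required. If power is restated, give it with its assumption from step 4 (0.84 or 0.78 at 42 per arm). Both figures are for 84 randomised, and keeping replacements would take the number above that.

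**Cost:** a change of wording, with no new data. The observed response rates will be slightly lower.
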